## Abstract

**Methods/design::**

This is a multicenter, randomized, double-blind, placebo-controlled trial. A total of 140 patients with cerebrovascular disorder and a history of aspiration pneumonia will be recruited from 6 centers and randomly assigned to either the real or sham press needle group in a 1:1 ratio. The press needle will be replaced twice a week. The treatment will be administered bilaterally at acupoints stomach meridian 36 and kidney meridian 3. The primary outcome is the frequency of aspiration pneumonia onset. The secondary outcome is the improvement of the latent time of the swallowing reflex. The study period is of 12-month. The primary outcome will be evaluated throughout the study period, while the secondary outcomes will be assessed at baseline, 1st month, 6th month, and at the end of the investigation period.

**Discussion::**

This study will evaluate the effects of press needle on the prevention of aspiration pneumonia and the improvement of swallowing function in patients. The results of this study will help support the prophylaxis of aspiration pneumonia.

## 1. Introduction (6a, 6b, 7, 8)

In Japan, pneumonia is the fifth most common cause of death worldwide. Moreover, 97% of the deaths due to pneumonia occur among older adults aged ≥65 years. In addition, the ratio of aspiration pneumonia to age-specific pneumonia increases with aging.^[1]^ Among patients with pneumonia aged ≥70 years, approximately 70% are considered to have aspiration pneumonia.^[2]^ Particularly, patients with cerebrovascular disorders are easily affected by aspiration pneumonia.^[3,4]^ In other words, aspiration pneumonitis is an important disease associated with vital prognoses in older adults. Aspiration pneumonia is caused by an influx of saliva and other fluids, particularly at night. A decrease in the swallowing reflex is strongly related to the onset of aspiration pneumonia.^[5]^ Furthermore, physiological changes associated with aging contribute to this decrease.^[6]^ The causes include a decrease in masticatory force due to missing teeth, poor alimentary bolus formation with decreased capacity of saliva secretion, delay in swallowing reflex creation with a decrease in pharyngeal perception, delay of the elevation by the low degree of the laryngeal prominence, and parorexia with a decrease in cognitive function.^[7,8]^ In addition, a history of cerebrovascular disorders results in a decrease in substance P, an important trigger for the swallowing reflex, and reduces swallowing function.^[9]^

Strategies for preventing aspiration pneumonia include improvement of swallowing function with rehabilitation, pharmacotherapy mouth care, prevention of gastroesophageal reflux, maintenance of consciousness, maintenance of nutritional status, and vaccination against pneumococcus.^[10]^ However, the number of patients with aspiration pneumonia has increased.^[1]^ Therefore, novel therapies that improve swallowing function and prevent aspiration pneumonia are required.

We previously reported improvements in swallowing function in older adults with cerebrovascular disorders using acupuncture stimulation.^[11–13]^ However, the protective efficacy of acupuncture stimulation against aspiration pneumonia has not yet been reported. This study aimed to investigate the protective efficacy of press needle stimulation in the lower limbs for aspiration pneumonia. This study will be a randomized double-blind placebo-controlled trial to assess the efficacy and safety of press needles for aspiration pneumonia and swallowing function in patients with cerebrovascular disease and a history of aspiration pneumonia. Participants will be blinded to the treatment assignment throughout the trial. The study design is illustrated in Figure 1.

**Figure 1. F1:**
[figure not shown]
Flow chart of the clinical trial. LTSR = latent time of swallowing reflex, BI = Barthel index, BMI = body mass index, LTSR = latent time of swallowing reflex, MMSE = mini-mental state examination.

## 2. Methods/design

### 2.1. Study setting (9)

Potential participants with cerebrovascular disease with a history of aspiration pneumonia will be recruited from the National Hospital Organization Yonezawa Hospital, Minamisanriu Hospital, Kesennuma City Motoyoshi Hospital, Saka General Hospital, Sendai Tomizawa Hospital, and Ikeno Clinic in Japan. The list of the institution is submitted to the Tohoku University clinical research Ethical Review Board and can obtain it from there.

### 2.2. Eligibility (10)

Older patients who met all of the following inclusion criteria and do not meet any of the listed exclusion criteria will be eligible to participate:

#### 2.2.1. Inclusion criteria.

Patients with cerebrovascular disease and a history of aspiration pneumonia.Patients in the life stage (maintenance or chronic stage) of rehabilitation for cerebrovascular disease.Patients of a joint research facility receiving in patient or home care.

#### 2.2.2. Exclusion criteria.

Patients with serious diseases, such as chronic respiratory diseases, malignancies, and chronic ischemic diseases, that can result in pneumonia.Patients with metal allergies.Patients with severe skin disorders.Patients with no developed swallowing reflex at the time of the initial latent time of swallowing reflex (LTSR) measurement.Patients with 3 or more severe aspiration pneumonia episodes in the past 3 months.

Patients receiving the standard treatment for cerebrovascular disease, its sequelae, and aspiration pneumonia are acceptable. However, the use of high-dose steroids and immunosuppressive therapies are unacceptable.

### 2.3. Interventions (11)

#### 2.3.1. Intervention description {11a}.

Participants will receive press needle stimulation at 2 acupuncture points, ST36 (Zusanli) and kidney meridian 3 (Taixi),^[14]^ on the lower limbs for 12 months. According to traditional Chinese medicine, stimulation of these 2 acupuncture points is beneficial for age-related decline in swallowing function. A press needle is a therapeutic device in which an acupuncture needle is safely secured using a circular surgical tape. Pionex Zero (Seirin Corporation, Shizuoka, Japan) noninvasive press needles will be used in this study (Fig. 2). The irritation area in contact with the skin is not a needle but a protrusion that is designed to not penetrate the skin. While the previous study used an invasive device,^[11]^ the present study used a safer device, considering the observation period of 12 months. The safety and quality of Pionex Zero are controlled by the Japanese Ministry of Health, Labour, and Welfare (Notification Number:22B1X00006000004). As a sham press needle was used for the control group, the protruding part of the Pionex Zero will be removed. The authenticity of the sham device has been confirmed.^[16]^ The press and sham press needles will be replaced twice weekly in the intervention and control groups.

#### 2.3.2. Criteria for discontinuing or modifying allocated interventions {11b}.

In cases of skin abnormality in the area of application of the press needles, physicians will be consulted and the intervention paused for a period of time. Subsequently, physicians will be consulted about the possibility of resuming treatment. The intervention will also be discontinued if other diseases develop during the period and require treatment.

#### 2.3.3. Strategies to improve adherence to interventions {11c}.

Frequent bedside visits and health assessments will be an important part of monitoring adherence.

#### 2.3.4. Relevant concomitant care permitted or prohibited during the trial {11d}.

Usual treatments for cerebrovascular disease, its sequelae, and aspiration pneumonia are acceptable. High-dose steroids and immunosuppressive therapy are unacceptable.

### 2.4. Outcomes (12)

The primary outcomes will help determine whether aspiration pneumonia is prevented and if press needle stimulation is effective. The primary outcome is the number of cases of aspiration pneumonia during the study period. Diagnosis of aspiration pneumonia will be made by the attending physician based on the Japanese Respiratory Society Guidelines for the management of hospital-acquired pneumonia in adults. The total number of diagnoses of aspiration pneumonia at the end of the study will be calculated.

Secondary outcomes will help determine whether seal acupuncture improves swallowing function and general conditions. The secondary outcomes are LTSR, fever frequency, Barthel index (BI), body mass index, general blood test results, and mini-mental state examination (MMSE) results. LTSR measures the time between the insertion of an 8 Fr tube through the nasal cavity to the uvula of the palate and the initiation of swallowing after the injection of 1 mL of distilled water. Three measurements are taken and the mean value is calculated. Fever is defined as a body temperature of 37.5°C or more. The number of days with fever during the study period will be determined.

### 2.5. Participant timeline (13)

The time schedule for this trial and data collection is summarized in Figure 2.

**Figure 2. F2:**
[figure not shown]
1. Way of applying Pionex Zero.^[15]^ The press needle used in this study is a Pionex Zero (Seirin Corporation, Shizuoka, Japan). The patented plastic case and sheath allow the practitioner to insert the needle without touching the needle tip or the surface of the Micropore™ adhesive tape. 2. Images of the press and sham press needle used in this study. The press needle has a non-sharp protrusion of 3 mm. In the sham press needle the protrusion is removed.

### 2.6. Sample size (14)

The sample size calculation is based on the results of previous studies. The incidence of aspiration pneumonia in previous studies was 0.091 (4/44) in the intervention group and 0.292 (14/48) in the control group.^[17]^ The sample size has been calculated with a 2-tailed significance level of 5% and a power of 80%, resulting in 118 participants (59 in each group). To account for 20 dropouts, the calculation 118 + 20 = 138 suggests that 138 patients should be recruited. This value has been rounded off to 140 patients.

### 2.7. Recruitment (15)

Potential participants with cerebrovascular disease and a history of aspiration pneumonia will be recruited from the National Hospital Organization Yonezawa Hospital, Minamisanriu Hospital, Kesennuma City Motoyoshi Hospital, Saka General Hospital, Sendai Tomizawa Hospital, and the Ikeno Clinic. The physician will contact the administrator when the patient meets the eligibility criteria. If participants are interested in our study, they will be informed of the purpose and content of the research as well as the benefits and drawbacks of participating in detail. After screening, the participants who meet the inclusion criteria will be enrolled. The study flow is shown in the SPIRIT Figure (Fig. 1). The participants will undergo a 12 months treatment period.

### 2.8. Randomization, allocation, and blinding (16)

#### 2.8.1. Method of generating the allocation sequence {16a}.

After obtaining written informed consent from the participants and baseline screening. Random numbers of 001 to 140 will be automatically generated by the SPSS software (whole random numbers). The participants will be randomly assigned to the intervention group or control group at a ratio of 1:1. An overview of the case distribution of each center, specific measurements, and time points of data collection can be found in the SPIRIT Figure (Fig. 3).

**Figure 3. F3:**
[figure not shown]
Measurement items and data collection plan. The number of occurrences of aspiration pneumonia and frequency of fever during the 12 months observation period will be determined. LTSR = latent time of swallowing reflex, BI = Barthel index, BMI = body mass index, LTSR = latent time of swallowing reflex, MMSE = mini-mental state examination.

#### 2.8.2. Mechanism of implementing the allocation sequence {16b}.

The random allocation sequence will be stored and concealed from the treating physicians, statisticians, and outcome assessors to prevent detection bias.

#### 2.8.3. Who will generate the allocation sequence{16c}.

The designated statisticians will generate the allocation sequence, and different investigators designated by the project leader will enroll or assign participants.

#### 2.8.4. Who will be blinded {17a}.

Information including the number of cases of aspiration pneumonia, LTSR, fever frequency, BI, body mass index, general blood sampling, and the MMSE will be assessed by independent assessors who are blinded to the assignment and treatment. The principal investigators, statisticians, and outcome assessors will be blinded to the treatment assignments until the database is locked.

#### 2.8.5. Procedure for unblinding if needed {17b}.

Unblinding the investigators will be permissible only in specific situations, such as when knowledge of the actual treatment is highly necessary for the appropriate management of participants (e.g., serious adverse events).

### 2.9. Data collection (18a, 18b)

An overview of specific measurements and time points for data collection is shown in the SPIRIT Figure (Fig. 3). All data will be collected and recorded on paper-based case report form (CRF) by the investigators. Patient characteristics, questionnaires, and evaluation forms, such as BI and MMSE, findings of LTSR swallowing measurement and number of incidences of aspiration pneumonia, fever frequency, laboratory data, and physical status will be collected. Adverse effects will also be recorded. After recording the data, the investigators will confirm the CRF form by referring to the medical records.

### 2.10. Data management (19)

We will assign identification code numbers to all participants. Upon registering and recording the CRF, personal identifying information (e.g., name, address, phone number, and medical record number) will be deleted from the data. A linkable anonymized number table will be created and stored by the data manager. All data will be kept in locked storage for at least 5 years after study completion. The data manager will confirm the CRF to check for duplication, missing information, and deviation from the data.

### 2.11. Statistical methods (20a, 20b, 20c)

#### 2.11.1. Statistical methods for primary and secondary outcomes (20a).

Statisticians will independently undertake statistical analyses. Parametric data will be presented as mean ± standard deviation, whereas non-parametric data as median and 95% confidence interval. Two-tailed *t* tests and chi-squared tests will be used to compare the demographic and clinical characteristics of the 2 groups at baseline. MMSE, BI, and total caloric intake at baseline and endpoint will be compared between the 2 groups using repeated-measures analysis of variance. The number of febrile days in the 2 groups was compared using the 2-tailed *t* test. The probabilities of being pneumonia-free and survival from pneumonia-related deaths will be estimated using the Kaplan–Meier product-limit method. Pneumonia-free survival rates will be calculated from the date of random assignment to the date of pneumonia onset, date of death, or cutoff date for patients alive at the time of closure of the dataset. A Cox proportional hazards regression model will be used to examine the relationship between modifiable factors and the incidence of pneumonia or pneumonia-related mortality. Relative risks) and 95% confidence interval will be calculated from 2-by-2 tables. Plausible predictors (age, sex, ease of diagnosis, duration of illness, activities of daily living, cognitive function, and treatment assignment) will be included in the original model. Backward stepwise regression will be performed, and *P* > .2 will be used for variable removal. Statistical analysis will be performed using SPSS software (version 21.0; IBM, Armonk, NY). All statistical tests will be 2-sided, and the statistical significance threshold will be set at 5%.

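### MMSE, Barthel index and caloric intake: repeated-measures ANOVA on baseline and endpoint treats the baseline as a response and names no tested term; baseline-adjusted ANCOVA is more precise on either reading

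*Protocol article*

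**What the plan says.** Section 2.11.1 fixes both the method and the time points: MMSE, Barthel index and total caloric intake "at baseline and endpoint will be compared between the 2 groups using repeated-measures analysis of variance". It does not say whether the treatment comparison is the group main effect or the group-by-time interaction. It sets a two-sided 5% level for all tests.

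Section 2.4 lists two of these three items as secondary outcomes: "The secondary outcomes are LTSR, fever frequency, Barthel index (BI), body mass index, general blood test results, and mini-mental state examination (MMSE) results". Total caloric intake is not on that list. On timing, the Abstract (Methods/design) says that "the secondary outcomes will be assessed at baseline, 1st month, 6th month, and at the end of the investigation period". The item-by-item schedule is in Figure 3, which is not shown in the text at hand.

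**The concern.** In a randomised trial the baseline is measured before treatment, so its expected between-group difference is zero. It carries no information on the effect as a response, but much information as a covariate, because it explains part of the spread in the endpoint. A two-point repeated-measures ANOVA uses it as a response.

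The consequence depends on the term that is read. The group-by-time term is a comparison of changes: valid, but less precise than covariate adjustment. The group main effect compares each patient's average of baseline and endpoint, so half of the quantity compared cannot respond to treatment, and the estimate targets half the endpoint difference. Because the article names neither term, two analysts could follow it faithfully and report different estimates and P values. At stake are the precision and meaning of the treatment comparison for these three items.

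**Working it through.** **The plan's own figure.** The only sample size given is for the primary outcome, from rates of "0.091 (4/44) in the intervention group and 0.292 (14/48) in the control group". The pooled-variance formula for two proportions is n = [1.960·√(2·p̄(1−p̄)) + 0.842·√(p₁(1−p₁)+p₂(1−p₂))]² / (p₁−p₂)². With 0.091 and 0.292 it gives 59 per group, or 118 in all, as stated in section 2.6. The unrounded fractions 4/44 and 14/48 give 60, and power at 59 per group is 79.96%. Adding 20 gives 138. The article states no power for MMSE, Barthel index or caloric intake.

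**Inputs.** From the documents: n = 59 evaluable per group, 1:1 allocation, two-sided 5%. Assumed: equal SD (set to 1) at both time points, baseline-endpoint correlation rho shown at 0.5, 0.7 and 0.8, and an endpoint effect δ in SD units. The normal approximation is used.

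**Formulas.** Each contrast has standard error √(2v/n), with:

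- ANCOVA on baseline: effect δ, v = 1 − rho²
- Group-by-time term (change score): effect δ, v = 2(1 − rho)
- Group main effect (mean of baseline and endpoint): effect δ/2, v = (1 + rho)/2

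The variance ratio of change score to ANCOVA is 2(1−rho)/(1−rho²) = 2/(1+rho). For the group main effect, after scaling to the same δ, it is 4·[(1+rho)/2]/(1−rho²) = 2/(1−rho). These ratios are also the factors by which the number of patients would have to grow to match ANCOVA.

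**Power when δ is set so that ANCOVA has 80%,** δ = (1.960 + 0.842)·√(2(1−rho²)/59):

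| rho | δ | ANCOVA | group-by-time | group main effect | patients needed, group-by-time | patients needed, main effect |
|---|---|---|---|---|---|---|
| 0.5 | 0.447 | 80% | 68% | 29% | 1.33× | 4.0× |
| 0.7 | 0.368 | 80% | 73% | 19% | 1.18× | 6.7× |
| 0.8 | 0.309 | 80% | 76% | 14% | 1.11× | 10× |

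Worked case at rho = 0.5. The standardised effect under ANCOVA is 2.802. For the group-by-time term it is 2.802·√(1.5/2) = 2.426, and 2.426 − 1.960 = 0.466 gives 68%. For the main effect it is 2.802·√(0.5/2) = 1.401, and 1.401 − 1.960 = −0.559 gives 29%. Because δ is tied to 80% ANCOVA power, these percentages do not depend on n.

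**Simulation check** (59 per group, t-based tests). At rho 0.5, 0.7 and 0.8, ANCOVA gave 78.2%, 79.3% and 78.9%; group-by-time 67.1%, 72.7% and 75.0%; main effect 28.9%, 19.1% and 13.8%.

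**Fixed effect of 0.5 SD instead,** 59 per group:

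| rho | ANCOVA | group-by-time | group main effect |
|---|---|---|---|
| 0.5 | 88% | 78% | 35% |
| 0.7 | 97% | 94% | 31% |
| 0.8 | 99.5% | 99% | 30% |

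The order of the three analyses is the same. With a highly stable measure the change score comes close to ANCOVA, while the main effect does not recover.

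**The case against.** The strongest defence is that group-by-time is the usual test in a pre/post repeated-measures ANOVA. On that reading the analysis is unbiased under randomisation, keeps its type I error and uses the baseline, only less efficiently than it could. Patients are in the maintenance or chronic stage (section 2.2.1), so MMSE and Barthel index may be stable, and at rho = 0.9 the change score needs only 5% more patients than ANCOVA. These are secondary outcomes with no power claim. All of this stands, and it limits the point to one of precision and an unnamed contrast.

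Four stronger readings are tempting, and the documents do not support them:

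- A reader might infer that the plan loses most of its power or wastes the baseline. The large loss arises only if the group main effect is tested, which the article does not say.
- A reader might infer that every functional secondary outcome is affected. The sentence covers three items. Swallowing-reflex latency and body mass index have no repeated-measures ANOVA assigned.
- A reader might infer that month 1 and month 6 values of MMSE and Barthel index are certainly collected and then discarded. That rests on the Abstract's general statement; comparing baseline and endpoint would also fit two measurements. With complete data those visits add almost nothing to a month-12 contrast.
- A reader might infer that sicker patients will be dropped and that deaths come on top of the planned loss. Section 2.6 allows for 20 dropouts in 138 (14.5%) without saying whether deaths are included or who leaves. Missing-data rules are commonly left to the analysis plan.

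Deferring the whole point to an analysis plan does not answer it, because section 2.11.1 already fixes the method and the two time points.

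**Conclusion.** The point holds as a matter of precision and clarity. On the milder reading the loss is modest: a variance 33%, 18% or 11% larger than ANCOVA's at rho 0.5, 0.7 or 0.8. On the other reading it is severe. Under the stated assumptions neither reading matches baseline adjustment at any rho below 1, so the preference for ANCOVA does not hang on which term was intended; only the size of the gain does.

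The figures rest on an assumed correlation, an assumed effect size and equal SDs at the two time points. The order of the three analyses is firmer than any single percentage. The conclusion covers MMSE, Barthel index and caloric intake only. It is a recommended improvement, not a flaw that threatens the trial's main result.

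**What to change.** In section 2.11.1, replace the repeated-measures ANOVA for these three items. State the month-12 between-group difference as the treatment contrast, and estimate it by ANCOVA with the baseline value as covariate, reported with its 95% confidence interval.

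For any of these items that is also measured at months 1 and 6, as the Abstract says of the secondary outcomes, use a mixed model on months 1, 6 and 12 with treatment, visit, treatment-by-visit and the baseline value, and report the month-12 contrast from it. Patients who leave before month 12 then still contribute their observed values. ANCOVA on month 12 alone does not do this, so the choice for each item should follow the visit schedule. Caloric intake is not on the section 2.4 list, so its visits need to be stated.

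The change needs no new data or patients and should be made before the database is locked. The cost is a revised sentence and slightly more modelling work.

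### Febrile days are compared as raw totals by t test with no allowance for time observed, so the comparison is biased if follow-up differs between the arms

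*Protocol article*

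**What the plan says.** Section 2.4 of the protocol article lists fever frequency among the secondary outcomes. It sets the threshold ("Fever is defined as a body temperature of 37.5°C or more") and the measure ("The number of days with fever during the study period will be determined"). The Figure 3 legend gives the window as 12 months. Section 2.11.1 then names the test: "The number of febrile days in the 2 groups was compared using the 2-tailed" t test. No denominator, rate, offset or rule for shortened observation is attached to this outcome.

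The same article expects observation to be cut short for some patients. Section 2.6 makes an allowance: "To account for 20 dropouts". Section 2.11.1 plans an analysis of pneumonia-related death and ends pneumonia-free survival at pneumonia onset, "date of death, or cutoff date for patients alive at the time of closure of the dataset". Time at risk is therefore handled for pneumonia, by Kaplan–Meier and Cox methods, but not for febrile days.

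**The concern.** A total of febrile days is bounded by the days on which the patient was observed. Someone who dies in month 2 can contribute at most about two months of fever and so enters a raw comparison as a good result. If such exits were equally common and equally timed in both arms, the two means would shrink by the same factor and their ratio would survive. If they are not, the comparison mixes the effect on fever with the effect on survival or retention.

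The trial hopes to prevent a disease that kills, so equal survival cannot be taken for granted. If the device prevents deaths, treated patients have more days in which to record a fever and the fever benefit is understated. If exits are heavier in the active arm, the error runs the other way and favours the device. A reader of the final report could not separate either from a treatment effect on fever.

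**Working it through.** **1. The plan's own figure.** The only sample size given is for the primary outcome. With p₁ = 0.091, p₂ = 0.292 (section 2.6), mean proportion 0.1915, two-sided 5% and 80% power:

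n = [1.96·√(2·0.1915·0.8085) + 0.8416·√(0.091·0.909 + 0.292·0.708)]² / 0.201² = (1.0907 + 0.4528)² / 0.0404 ≈ 59 per group, 118 in total.

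This reproduces the stated figure and does not depend on the fever analysis. No mean, SD, effect or power is given for febrile days, so there is no fever figure to reproduce. The dropout allowance is 20/138 = 14.5%, not split by arm.

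**2. The bias.** Let λ be the febrile-day rate per year and T the observed fraction of the year, unrelated to each other within an arm. The expected total is λ·E[T], so

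ratio of raw means = true rate ratio × E[T active] / E[T control].

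If a fraction q exits at a uniformly distributed time, E[T] = 1 − q/2. The values of q below are assumptions.

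| Exits, control vs active | Factor | True 0.50 becomes | True 1.00 becomes |
|---|---|---|---|
| 30% vs 10% | 0.95/0.85 = 1.12 | 0.56 | 1.12 |
| 20% vs 10% | 0.95/0.90 = 1.06 | 0.53 | 1.06 |
| 15% vs 10% | 0.95/0.925 = 1.03 | 0.51 | 1.03 |
| equal | 1 | 0.50 | 1.00 |
| 10% vs 30% | 0.85/0.95 = 0.89 | 0.45 | 0.89 |

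**3. Power and type I error, by simulation.** Assumed: 60 per arm, control mean 20 febrile days per year, between-patient gamma shape 0.6, uniform exit times. The t test on raw totals is set against a rate comparison with robust standard errors.

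- Fever halved, deaths 30% vs 10%: power 58% (t test) against about 79%.
- Fever halved, deaths 20% vs 10%: about 68% against 80%.
- Fever halved, equal exits: the t test loses about 4 to 5 points.
- No fever effect: t-test type I error is about 7% at 30% vs 10%, and near 5% at 20% vs 10% or 15% vs 10%.

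The robust rate comparison itself runs at about 6% under no effect, so its power is slightly flattered.

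**4. A second set of assumptions.** 70 per arm, control mean 10 days per year, dispersion 1.5, constant exit hazard, negative binomial likelihood-ratio test with offset.

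- True ratio 0.6, exits 30% control vs 10% active: raw ratio 0.67 and t-test power 38%; with offset, 0.60 and 65%.
- No effect, exits 10% control vs 30% active: raw ratio 0.88 and t-test rejection 8.4%; with offset, 0.99 and 4.5%.
- True ratio 0.6, equal 15% exits: 58% against 62%. At dispersion 3: 33% against 39%.
- True ratio 0.6, everyone followed for 12 months: 64% against 65%. At dispersion 3: 38% against 41%.

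Both sets point the same way: differential observation time does the damage, and the shape of the distribution adds little.

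**The case against.** The strongest objection is to size. No mortality figure appears in the article, and a 20-point gap is extreme. The source study in section 2.6 had pneumonia in 29.2% against 9.1%, so nearly every prevented pneumonia would have to be one that would have killed. This stands: the 30% versus 10% case is an upper scenario, and at 15% versus 10% a true 0.50 moves only to 0.51.

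A reader might infer that the t test could reverse a real benefit. The calculations do not show this. With fever halved, no significant result in the simulation favoured sham. A raw ratio above 1 arose only where there was no benefit to lose.

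A reader might also infer that the t test is invalid because the count is skewed. The article gives no distribution, so the skew is assumed. With equal follow-up the type I error is near 5% and the power loss is a few points.

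It can be said that section 2.11.1 does not state that dropouts enter with truncated totals, and that recruiting extra patients may mean that dropouts are not analysed. That is possible, but it does not settle how patients who die are counted. Likewise, stopping the intervention for another illness (section 2.3.2) is not stated to end observation and is not counted here as an exit.

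Finally, the simulated data suit the proposed model, with fever unrelated to death. If fever clusters before a fatal pneumonia, an offset does not remove the resulting truncation. This stands and shapes the fix.

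**Conclusion.** The point holds as a mismatch between a stated endpoint and a stated test. Both are fixed in the article, so it is not a detail left to an unseen analysis plan. The raw comparison is biased by the ratio of mean observed time, and the bias is zero if the arms are observed equally long. Under the first set of assumptions it ranges from none (equal exits) through 0.53 for a true 0.50 (20% versus 10%) to 0.56 (30% versus 10%), with a power deficit of about 4 to 5, 12 and 21 points respectively. False-positive inflation is modest and confined to large imbalance. Every febrile-day and mortality input is assumed. Confidence is high in the direction of the bias and low in its size in this trial. The outcome is secondary, so a change is advisable rather than essential.

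**What to change.** In section 2.11.1, replace the t test for febrile days by negative binomial regression with robust standard errors, treatment as the covariate, and as offset the log of days observed from randomisation to death, withdrawal or month 12. Report the rate ratio with its 95% CI. Report deaths by arm beside it, because the offset does not correct for death that is related to fever. State whether patients who withdraw contribute their observed days.

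The cost is small: a few sentences, plus an end-of-observation date on the case report form. The survival analysis already needs randomisation, death and cutoff dates. Section 2.9 lists fever frequency but no count of days with a temperature recorded, and section 2.2.1 admits home-care patients. If days measured differ from days enrolled, the form should capture days measured and the offset should use them. The change should be made before unblinding. The sample size does not change.
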